
### Patient informed consent

Since the study includes a particular and vulnerable population, often not being able to give consent themselves due to, for example, sedation, there is a defined approach to obtain informed consent.

Whenever a potential study participant will not be capable to give his/her consent for the study themselves because of intubation or general restricted constitution, an independent auditing physician, acting as the patient’s representative, will declare the patient’s suitability for trial participation in the patient’s name. The signed document of the independent physician will be the prevailing condition for including the patient in the study. As soon as possible, a member of the study team will talk to the patient’s next of kin or preferably to the patient him/herself and explain the nature of the study, its purpose, the procedures involved, the expected duration, the potential benefits and risks and any discomfort it may entail. The patient or his/her next of kin will be informed that the participation in the study is voluntary and withdrawal from the study is possible at any time and that withdrawal of consent will not affect the subsequent medical assistance and treatment. The patient’s next of kin will be advised to decide according to the patient’s presumed will. If possible, formal consent from a participant’s next of kin, using the approved consent form, must be obtained before the participant is subjected to any study procedure. As soon as feasible, written informed consent from the patient him/herself must be obtained. Wherever possible, the participant or the next of kin must be informed that authorised institutions other than their treating physicians may examine the medical record.

A participant information sheet will be given to all consenting participants and to consenting next of kin deciding in their relative’s behalf. This information sheet describes the study and provides sufficient information for the participant and his/her next of kin to make an informed decision about the participation in the study. There will be a consent form for the patient and a secondary form for the patient’s next of kin. The patient and next of kin information sheet and the consent forms have been submitted to the competent ethics committee for revision and have been approved.

If possible, the patient or the next of kin should read and consider the statement before signing and dating the informed consent form and will receive a copy of the signed document. The consent form signed by the patient and/or his/her next of kin must also be signed and dated by a member of the study team. The original signed form will be stored along with the study-specific documents.

Whenever the participant or the patient’s next of kin refuses or withdraws his/her consent, the patient will immediately be excluded from any study interventions.

### Model consent form and other related documentation given to participants and authorised surrogates

These documents are available from the corresponding author on request.

### Additional consent provisions for collection and use of participant data and biological specimens

As stated previously, in the consent form, participants will be asked if they agree to use of their data should they choose to withdraw from the trial. Participants will also be asked for permission for the research team to share relevant data with people from the Universities taking part in the research or from regulatory authorities, where relevant. This trial involves collecting biological specimens for storage.

### Interventions

#### Explanation for the choice of comparators

Continuous enteral feeding represents current standard and will serve as the direct comparator to the intervention with intermittent feeding. Our trial will examine two different application protocols with high-protein enteral feeding.

#### Intervention description

In both the experimental (IF) and control (CF) groups, the high-protein (i.e. 10 g protein per 100 ml; 1.13 g leucine/100 ml) whey-based formula Fresubin© Intensive (Fresenius Kabi Schweiz AG) will be administered by nasogastric tube. Fresubin© Intensive is a specific enteral formula used in critically ill patients during acute phase to deliver a high amount of protein. A detailed list of ingredients can be found in Supplementary Table 1. Based on expert consensus, in the absence of indirect calorimetry (IC), we suggest that a published predictive equation or a simplistic weight-based equation (25–30 kcal/kg/day) be used to determine energy requirements. Dose and administration regime are indicated in Table 1 for the experimental group and in Table 2 for the control group.

**Table 1 Tab1:** Intermittent feeding protocol (experimental group)

Time	06:00–06:30		10:30	11:00–11:30		15:30	16:00–16:30		20:30	21:00–21:30		01:30	
	Nutrition	Break	GRV	Nutrition	Break	GRV	Nutrition	Break	GRV	Nutrition	Break	GRV	Break
**Day 1**													
Protein dose^1^	0.1			0.2			0.4			0.4			
Flow rate^2^	50–90			100–180			200–360			200–360			
Total protein^3^	0.1			0.3			0.7			1.1			
**Day 2**													
Protein dose^1^	0.4			0.4			0.4			0.4			
Flow rate^2^	200–360			200–360			200–360			200–360			
Total protein^3^	1.4			1.6			1.6			1.6			

*GRV* gastric residual volume

^1^[g/kgBW/30 min], 4 nutrition cycles/24 h: each with 30 min nutrition followed by a 4-h break and 30 min GRV measure, night time break of 4 h. Total time of feeding, 2 h; GRV measurements, 2 h; break, 20 h

^2^[ml Fresubin© Intensive/30 min], depending on bodyweight

^3^Total of administered protein of the preceding 24 h [g/kgBW]

**Table 2 Tab2:** Continuous feeding protocol (control group)

Time	06:00–11:00	11:00–12:00	12:00–17:00	17:00–18:00	18:00–23:00	23:00–00:00	00:00–05:00	05:00–06:00
	Nutrition	Break + GRV	Nutrition	Break + GRV	Nutrition	Break + GRV	Nutrition	Break + GRV
**Day 1**								
Protein dose^1^	0.05		0.1		0.2		0.3	
Flow rate^2^	5–9		10–18		20–36		30–54	
Total protein^3^	0.05		0.15		0.35		0.65	
**Day 2**								
Protein dose^1^	0.4		0.4		0.4		0.4	
Flow rate^2^	40–72		40–72		40–72		40–72	
Total protein^3^	1.0		1.3		1.5		1.6	

*GRV* gastric residual volume

^1^[g/kgBW/5 h], 4 nutrition cycles/24 h: each with 5 h nutrition followed by a 30-min break and 30 min GRV measure, no night time break. Total time of feeding, 20 h; GRV measurements, 2 h; break 2 h

^2^[ml Fresubin© Intensive/h], depending on bodyweight

^3^Total of administered protein of the preceding 24 h [g/kgBW]

The experimental group will receive a calculated amount of enteral nutrition over 30 min, whereas the control group will receive the same amount over 5 h. After a 4.5-h break in feeding in the experimental group and a 1-h break in feeding in the control group, the next feeding cycle will begin. The experimental group will have a 4-h break at night.

The experimental group will start with 0.1 g protein/kg BW and will receive 0.2 g protein/kg BW in the next cycle, which again will be doubled within the third cycle to 0.4 g protein/kg BW. The control group will start with 0.05 g protein/kg BW. With the second cycle, patients receive 0.1 g protein/kg BW with further increase by 0.1 g protein/kg BW with every cycle until the amount of 0.4 g protein/kg BW is achieved. The protein target will be reached at the cumulative dose of at least 1.5 g protein/kg BW/24 h over 4 consecutive feeding cycles.

For calculation of our protein targets of participants with BMI > 18 to < 30, the actual body weight will be used. For participants with a BMI of 30–34.9 kg/m^2^, the target protein amount will be matched for an ideal weight with a BMI of 25 kg/m^2^. Hence, indicated flow rates in Tables 1 and 2 are calculated based on protein targets which are prioritised to energy targets during the acute phase of ICU stay.

#### Criteria for discontinuing or modifying allocated interventions

Participants will be withdrawn from the study in case of the following:
Death or rapid recovery/dischargeOn demand of the patient or his/her next of kinOn demand of the treating physician or the study team (e.g. safety reasons, please see the “Adverse event reporting and harms” section)

#### Strategies to improve adherence to interventions

To improve adherence to intervention protocols and monitoring adherence, all study patients receive a bedside protocol with the study group, feeding cycles and calculated amount of nutrition, space for documentation of adverse events within every nutrition cycle. The study team fulfils daily controls and if needed reminds bedside nurses to document all the values needed for the study.

#### Relevant concomitant care permitted or prohibited during the trial

Implementing intermittent and continuous enteral nutrition with a protein-rich formula in critically ill patients will not require alteration to usual care pathways (including use of any medication), and these will continue for both trial arms.

#### Provisions for post-trial care

All participants will be monitored independent from the study according to ICU standards. Participants experiencing pulmonary aspiration during the study period will be followed up until hospital discharge. Apart from time to ICU discharge, potential complications of aspiration until hospital discharge—such as pneumonia, empyema, lung abscess, pleural effusion, sepsis and acute respiratory distress syndrome (ARDS)—will be registered.

#### Outcomes

##### Primary outcome measure

The primary outcome is the time in hours from the first study-specific administration of enteral nutrition until individual protein target quantity of at least 1.5 g protein/kg BW/24 h is reached. The daily protein target quantity is relative to the bodyweight and therefore varies among patients. According to the ASPEN guidelines for the ICU enteral nutrition [35], our target is 1.5 g protein/kg BW/24 h and should be reached in acute phase nutrition of critically ill patients.

##### Secondary outcome measures

The following secondary outcome measures will be assessed to detect differences among both feeding protocols:
Evolution of values (i.e. the trend of the assessed parameters during the 7-day study period) for anabolic and catabolic pathways (ubiquitin-proteasome and autophagy) which control muscle metabolism as identified by proteomic analysis of vastus lateralis muscle biopsies prior to the start of nutrition and on day 7 in both study groupsQuadriceps muscle area and diameter by ultrasound prior to start of nutrition and on day 7 in both study groupsAmount of gastric residual volume (GRV) in millilitres per day and assessed after every nutrition cycleNumber of events of diarrhoea, constipation, meteorism, nausea, regurgitation, vomiting and pulmonary aspiration per feeding cycle:
Acute diarrhoea over ≥ 3 unformed to liquid bowel movements within 24 h and with a total weight of > 250 g per day are present.Constipation is diagnosed if the defecation is more difficult and takes place less than three times a week; in the study, constipation will be defined at ≥ 3 days without bowel movements, whereby investigators must influence the stool regulation with medication.Amount of regurgitation in millilitres per day and assessed after every nutrition cycle.Assessment of glucose values (mmol/l) for assessment of effect on glucose metabolismAssessment of urea (mmol/l) once daily as a marker for amino acid degradationAssessment of IGF-1 (insulin-like growth factor 1) once daily due to its influence on the MPS pathwayAssessment of Acute Physiology and Chronic Health Evaluation (APACHE II; for severity of disease) and Simplified Acute Physiology Score (SAPS II; for risk of mortality) upon study inclusion (baseline), and daily assessment of Sepsis-related Organ Failure Assessment (SOFA; for degree of organ dysfunction)Nutrition Risk in Critically Ill (NUTRIC) score including interleukin-6 upon study inclusion (baseline)

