##### Study period

The study period is 7 days beginning with the initiation of enteral feeding.

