##### Day of inclusion (t_−1_)

We plan to perform the ultrasound and muscle biopsy on the day of study inclusion of eligible patients. Depending on time of ICU admittance, staff resources and opening hours of the Biobank storage, we will not always be able to do so. Therefore, if both the ultrasound and biopsy can be performed before 3:00 pm on the day of inclusion, enteral feeding will be initiated the next morning at 6:00 am. Otherwise, the procedures will be postponed to the next day and start of enteral feeding will be the following morning at 6:00 am. All standard laboratory parameters plus IGF-1 and interleukin-6 (for NUTRIC score) will be measured along with the morning routine laboratory of the next day. APACHE II, SAPS II and SOFA scores will be assessed within the first 24 h after ICU admission.

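### Diarrhoea and constipation are tallied per feeding cycle although they are defined over 24 h and at least 3 days, and constipation dating from before the first study feed can enter the tolerance comparison

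*Protocol article*

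**What the plan says.** The list under Secondary outcome measures makes the feeding cycle the counting unit for seven tolerance events, diarrhoea and constipation among them. It then defines these two over longer windows. Diarrhoea needs at least three "unformed to liquid bowel movements within 24 h and with a total weight of > 250 g per day are present". For constipation, "in the study, constipation will be defined at ≥ 3 days without bowel movements", followed by the clause "whereby investigators must influence the stool regulation with medication".

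Both arms have four cycles a day. The footnote to Table 1 gives "4 nutrition cycles/24 h: each with 30 min nutrition followed by a 4-h break" for intermittent feeding (IF), and the footnote to Table 2 gives "4 nutrition cycles/24 h: each with 5 h nutrition followed by a 30-min break" for continuous feeding (CF). On duration, "The study period is 7 days beginning with the initiation of enteral feeding". The bedside sheet described under Strategies to improve adherence to interventions has "space for documentation of adverse events within every nutrition cycle".

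Enrolment may be up to 48 h after ICU admission (Eligibility criteria; Participant timeline). If biopsy and ultrasound are done before 3:00 pm on the day of inclusion, feeding starts the next morning. The section Day of inclusion continues: "Otherwise, the procedures will be postponed to the next day and start of enteral feeding will be the following morning at 6:00 am".

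Primary and secondary analysis applies two-way repeated-measures ANOVA, with comparisons at each time point, to all secondary outcomes.

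**The concern.** A cycle lasts about 6 h, while the two definitions span 24 h and at least 72 h. Neither state can be established within one cycle, and both can persist over many. The protocol does not say whether a nurse who finds the state still present enters it again at the next cycle. The tally may therefore reflect how long a state lasted and how it was recorded, as well as how often it arose.

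The stool-free clock also has no stated starting point. A patient without stool since admission may reach 3 days before receiving any study feed. That constipation cannot have been caused by the feeding regimen, yet nothing in the text removes it from the tally.

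At stake is the tolerance comparison. The introduction expects IF to be tolerated as well as CF, and the Discussion (Outcomes) gives comparison of tolerance as the purpose of the secondary outcomes. Events unrelated to the regimen, occurring alike in both arms, add variance and dilute any real difference.

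**Working it through.** **1. Number of cycles.** Sample size states 20 time points: 4 per day × 5 days = 20, reproduced. Over the 7-day study period, 4 × 7 = 28. In cycles, the diarrhoea window is 4 long and the constipation window is 4 × 3 = 12 long.

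**2. Cycle ends, from the clock times in Tables 1 and 2.** In hours after 06:00 each day, cycles end at 5, 10, 15 and 20 (IF) and at 6, 12, 18 and 24 (CF), including the residual-volume check. Counted from the first feed:

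- Cycle 12 ends at 48 + 20 = 68 h (IF) or 48 + 24 = 72 h (CF).
- Cycle 13 in IF ends at 72 + 5 = 77 h.

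If the last stool coincides with the first feed, 72 h is reached at the end of cycle 12 in CF and in cycle 13 in IF. Any constipation entered in cycles 1–11 (CF) or 1–12 (IF) must therefore rest on a stool-free interval that began before the first feed. That is 11 or 12 of the 20 time points used for the sample size. This step needs no assumption about repeat entry.

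**3. Score of one constipation episode.** Assumption for the last four rows: the state is entered at every cycle end at which at least 72 h have passed without stool, and any medication condition is already met.

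| Case | IF | CF |
|---|---|---|
| Entered once, at onset | 1 | 1 |
| Last stool at first feed, next stool at 96 h | 4 | 4 |
| Last stool at first feed, next stool at 120 h | 8 | 8 |
| Last stool at first feed, none to day 7 | 28 − 12 = 16 | 28 − 11 = 17 |
| Last stool 72 h before first feed, none to day 7 | 28 | 28 |

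**4. Score of one isolated diarrhoea episode.** Assumption: the 24-h look-back is applied at each cycle end. The state then holds for 24 h minus the time between the first and third stool.

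- Three stools spanning 3 h: 24 − 3 = 21 h. At 4 cycle ends per 24 h this gives 21 × 4/24 = 3.5 entries on average (3 or 4).
- Second and third stools uniform over the 24 h after the first: mean span 16 h, leaving 8 h, so 8 × 4/24 = 1.33 entries on average. Simulation gave 1.33 in both arms, range 0 to 4.
- Entered once at onset: 1.

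**5. Time from admission to first feed.**

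- Shortest delay from inclusion, with procedures done just before 3:00 pm: 9 + 6 = 15 h.
- Longest, with inclusion just after midnight and procedures postponed to the next day: 24 + 24 + 6 = 54 h. From admission, 48 + 54 = 102 h.
- Narrower reading, with postponement only for inclusion after 3:00 pm: 9 + 24 + 6 = 39 h. From admission, 48 + 39 = 87 h.

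Both maxima exceed 72 h, even when the stool-free clock starts only at ICU admission.

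**The case against.** The unit is a number of events per cycle, which can be read as entering an event once, in the cycle where it is diagnosed. Space on a sheet for each cycle is not an instruction to re-enter a continuing state. This stands: the high scores depend on a recording rule that the protocol does not state, and onset recording gives 1.

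The medication clause, if read as a criterion, means that 72 h without stool is not enough. This also stands, and it makes 16, 17 and 28 maxima. It does not affect step 2, because a further condition can only delay the time at which the definition is met.

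A reader might infer that pre-feed constipation is prescribed as a tolerance event. The documents do not say so. Table 3 marks secondary variables, including side-effect documentation, at screening. The section on GRV and side effects speaks of effects caused by the formula, and Adverse event reporting of events related to feeding. But none of these gives an attribution criterion or a rule for a condition already present, so such constipation can be counted.

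A reader might also infer bias towards one arm, or a total score swamped by constipation. Neither is supported. Both arms have four cycles a day and start at 06:00, the maxima are nearly equal (16 against 17), and randomisation balances prior constipation in expectation. No passage sums the event types.

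Finally, detailed methods are left to a statistical analysis plan that is not shown, and a counting rule may be there. However, the protocol itself fixes the per-cycle unit, and that unit fits these two definitions poorly whatever detail is added later.

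**Conclusion.** The point holds for two secondary tolerance items. The stated unit does not match the definitions of diarrhoea and constipation. One episode may score from 1, if recorded at onset, to 16–17, if constipation is re-entered every cycle after a last stool at the first feed. The extreme of 28 needs three things together: the criterion already met at the first feed, no stool for 7 days, and entry at every cycle.

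Separately from repeat entry, constipation recorded before the end of cycle 12 (CF) or before cycle 13 (IF) must have begun before study feeding. The timetable allows this, with up to 102 h (87 h on the narrower reading) from admission to first feed.

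The consequence is added noise and a diluted comparison for these two items. The loss of precision cannot be quantified, because the protocol gives no event rates. No directional bias is shown. The primary outcome and the sample size are unaffected. The change is worth making but not critical.

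**What to change.** For diarrhoea and constipation only, replace the per-cycle count by two patient-level measures:

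- new onset after the first study feed, yes or no;
- patient-days with the condition, at most 7 instead of 28 cycle entries, read against the days actually observed.

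Flag patients who already meet the constipation criterion at the first feed as prevalent, and leave them out of the new-onset comparison. State whether the medication clause is part of the definition. Keep per-cycle counts for discrete events such as vomiting, regurgitation and aspiration.

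The cost is a change of wording and a derivation from the bedside and screening records, with no new measurements. The small downside is that patients constipated at the first feed do not contribute to the new-onset comparison.

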#### Participant timeline

The study period consists of screening and enrolment, allocation, observation time and closeout. Screening and enrolment will be performed within 48 h after ICU admission. Allocation is defined as the day of start of enteral feeding. Closeout is defined as the end of the seventh day of observation (or day of discharge from the ICU, if earlier than 7 days).

##### Study period

The study period is 7 days beginning with the initiation of enteral feeding.

##### Study schedule

Study flow is shown in Fig. 1 and Table 3.

**Fig. 1 Fig1:**
[figure not shown]
Study Flow Chart

**Table 3 Tab3:** Study schedule

	Screening	Allocation	Observation time					Closeout
Time	t_−1_	t_0_	t_1_	t_2_	t_3_	t_4_	t_5_	t_6_
Day	0	1	2	3	4	5	6	7
Eligibility criteria	x							
Informed consent	x							
Randomisation	x							
Baseline data	x							
Muscle biopsy and ultrasound	x^1^							x
Start feeding		x^2^						
Vital parameters	x	x	x	x	x	x	x	x
Primary variables		x	x	x	x	x	x	x
Secondary variables^3^	x	x	x	x	x	x	x	x
SAEs		x	x	x	x	x	x	x

^1^Performance of muscle ultrasound and biopsy on inclusion day until 3:00 pm will allow enteral feeding starting the next day at 6:00 am. Whenever the study team is not able to perform both before 3:00 pm, these study procedures will be postponed to the next day and study feeding will start the day after at 6:00 am

^2^6:00 am

^3^Including laboratory parameters, documentation of side effects of enteral feeding and assessment of SOFA score

##### Day of inclusion (t_−1_)

We plan to perform the ultrasound and muscle biopsy on the day of study inclusion of eligible patients. Depending on time of ICU admittance, staff resources and opening hours of the Biobank storage, we will not always be able to do so. Therefore, if both the ultrasound and biopsy can be performed before 3:00 pm on the day of inclusion, enteral feeding will be initiated the next morning at 6:00 am. Otherwise, the procedures will be postponed to the next day and start of enteral feeding will be the following morning at 6:00 am. All standard laboratory parameters plus IGF-1 and interleukin-6 (for NUTRIC score) will be measured along with the morning routine laboratory of the next day. APACHE II, SAPS II and SOFA scores will be assessed within the first 24 h after ICU admission.

